#### Knowledge assessment

2.6.11.

To ascertain the extent of knowledge enhancement pertaining to survival responses following the intervention, participants will be required to complete a brief knowledge questionnaire both prior (T1) to and subsequent to the intervention (T2 or T3). The internally devised questionnaire comprises six items structured on a 7-point Likert scale. Participants are afforded the opportunity to express their level of agreement or disagreement with statements, ranging from complete agreement to complete disagreement, or any point in between. Statements include assertions such as ‘Freezing or immobilization is an automatic response under stress that one cannot control’ and ‘During instances of physical/sexual violence or sexual abuse, automatic bodily reactions occur with the aim of survival, over which the individual possesses minimal control.

### Data analyses

2.7.

The G*Power programme (version 3.1.9.2) was used to calculate the sample size. An a priori power calculation showed that the proposed RCT sample required 34 participants (*n* = 17 for each condition). Calculations in G*Power (Cohen’s *d* = 0.5; equivalent of *f* = 0.25 ANOVA) showed that a sample size of *n* = 17 for each group had sufficient power (80%) to reject our null hypothesis, namely, that there was no difference between the two conditions. A between groups effect size of Cohen’s *d* of 0.50 is considered a medium effect size. In a comparable study (Boulton & Boulton, 2017), the between group pre–post effect size on self-blame was very large (*d* > 1.2) and the sample size was also comparable. Based on this study, we believe that the expected effect size (Cohen’s *d*) of .50 in our study is reasonable.

Data will be analyzed using SPSS V.24.0 for Windows (SPSS Incorporated). Descriptive statistics will be calculated for the baseline characteristics of the study population. Parametric data are presented as means with standard deviations (SD), and nonparametric distributed variables as medians with Inter Quartile Ranges (IQRs). The intervention effect will be evaluated for group differences between Condition 1 (intervention) and Condition 2 (waiting-list control group). The primary outcome measure is feelings of shame and guilt, as measured with the SGATS. We will use a will be tested using an two-way repeated measures ANOVA test to determine whether any change in response to the SGATS (i.e. the dependent variable) is the result of interaction between the ‘type of treatment’ (i.e. the waiting-list control group or Intervention group, which is one of our two factors) and ‘time’ (i.e. our second factor T1 and T2). Statistical significance was set at *P* < .05. The secondary outcome measures included the severity of posttraumatic cognition symptoms, posttraumatic stress symptoms, anxiety, mood symptoms, and changes in motivation for trauma-focused treatment and disclosure. Changes between the groups at pre-test and post-test will be tested using ANOVA, while correcting for multiple testing.

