When meeting the inclusion criteria, the participants will receive a letter with information about the intervention, study, and informed consent form. Parents (or legal guardians) from participants between the ages of 12 and 16 years will also receive a letter with information and will be asked for permission. Each participant can individually start with the intervention whenever they are ready. After inclusion and obtaining informed consent, participants will have one week to complete the baseline questionnaires (T1). Once they completed the baseline questionnaires, the randomization procedure will start. Participants will be randomly allocated to the intervention or waiting-list control groups. The Castor EDC will be used as a random-number generator. A 1:1 allocation ratio will be applied. We utilize block randomization with varying block sizes for this purpose, stratifying for the following variables: gender (boy, girl), type of trauma (physical violence, sexual abuse), and frequency of trauma (single occurrence, multiple occurrences) to ensure that the number of participants is well balanced across both treatment arms within each stratum. Randomization results will be communicated to the participants and their parents (or legal caretakers) via e-mail or phone calls. After the randomization procedure, participants will receive login codes on a website where they can engage in the online psychoeducation programme. The website is available through a login, which allows the research team to evaluate the parts of the website that have been visited and the time spent on the webpage. After two weeks, measurements will be taken (T2) for both groups. After T2, the participants referred to the waiting-list control group will receive access to the online psychoeducation programme. Two weeks after access, post-intervention measurements will be conducted (T3) for the waiting-list control group. Completing the questionnaires takes approximately 15–30 min per assessment. There are no costs incurred by the participants. Participants who dropout before the start of the intervention from the study will be replaced by new participants, with a maximum of 20% of all participants. Participants who dropout during the intervention will not be replaced.

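### The stated 80% power for a between-group d of 0.50 with 17 per arm does not follow: it is about 29% if the T1–T2 correlation is 0.5, and 34 participants give 80% power only for d of about 1.0

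*Protocol article*

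**What the plan says.** The sample size rests on one paragraph of section 2.7 (Data analyses) of the protocol article.

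- Size: "the proposed RCT sample required 34 participants (*n* = 17 for each condition".
- Effect-size input: "Calculations in G*Power (Cohen’s *d* = 0.5; equivalent of *f* = 0.25 ANOVA".
- Claim: "a sample size of *n* = 17 for each group had sufficient power (80%) to reject our null hypothesis". The null hypothesis is described as "namely, that there was no difference between the two conditions".
- Meaning of the effect size: "A between groups effect size of Cohen’s *d* of 0.50 is considered a medium effect size".
- Expectation for this trial, after citing a comparable study with d above 1.2: "we believe that the expected effect size (Cohen’s *d*) of .50 in our study is reasonable".

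The same section makes the primary test the group-by-time interaction of a two-way repeated measures ANOVA on the SGATS, with T1 and T2 as the two times and significance at P < .05. It states neither the G*Power routine nor a correlation between T1 and T2. Section 2.4 (Procedure) sets 1:1 allocation, allows replacement (up to 20%) of those who leave before the intervention starts, and adds: "Participants who dropout during the intervention will not be replaced".

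**The concern.** Detecting a between-group d of 0.50 with 80% power in a plain two-group comparison takes about 64 per arm, so 17 per arm is far too few unless repeated measurement adds a great deal of precision. The conversion from d to f is the likely weak point. The relation d = 2f belongs to two groups measured once, whereas the planned test is an interaction in a two-by-two layout, where the same f stands for a larger difference.

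This paragraph is the only justification of the sample size, and it concerns the primary outcome. The Discussion makes public release of the programme depend on the trial showing a reduction in shame and guilt. A reader who takes the 80% at face value will misjudge what a non-significant result can tell them.

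**Working it through.** **Inputs.** From 2.7: d = 0.50, f = 0.25, N = 34 (n = 17 per arm), m = 2 times, k = 2 groups, alpha 0.05. The ANOVA F test is non-directional, so this matches a two-sided t test. Assumed, because the article gives none: the T1–T2 correlation ρ, shown over a range.

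**Step 1: reproduce the 34.** For the within-between interaction, λ = f²·N·m/(1 − ρ), with 1 and N − 2 degrees of freedom. With f = 0.25 and ρ = 0.5:

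- N = 34: λ = 0.0625 × 34 × 2 / 0.5 = 8.5, F(1, 32), power 0.807
- N = 32: power 0.781

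So 34 is the smallest balanced size that reaches 80% by this route, which is also the planned test. That this routine was the one used is an inference.

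**Step 2: what f = 0.25 means there.** Take equal baselines and a T2 difference of d SDs. The cell means are (0, −d) and (0, 0), and each of the four interaction terms has size d/4. Hence f = d/4:

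- f = 0.25 gives d = 4 × 0.25 = 1.0
- d = 0.50 gives f = 0.50/4 = 0.125

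Check: a t test on change scores with a difference of 1.0 SD and ρ = 0.5 gives the same 0.807.

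**Step 3: power for d = 0.50 when the groups are compared once.** Here d = 2f does hold. The noncentrality is 0.5 × √(17/2) = 1.458 on 32 degrees of freedom. Power is 0.293 two-sided and 0.414 one-sided. For 80% power two-sided, 64 per arm are needed.

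**Step 4: power for d = 0.50 in the planned test.** With f = 0.125, λ = 0.015625 × 34 × 2/(1 − ρ) = 1.0625/(1 − ρ).

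| Assumed ρ | λ | Power at d = 0.50 (raw-score SDs) |
|---|---|---|
| 0 | 1.06 | 0.17 |
| 0.3 | 1.52 | 0.22 |
| 0.5 | 2.13 | 0.29 |
| 0.7 | 3.54 | 0.45 |
| 0.8 | 5.31 | 0.61 |
| 0.87 | 8.17 | 0.79 |

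Power crosses 80% at ρ of about 0.873. A simulation of 100,000 trials at ρ = 0.5 gave 0.297. At ρ = 0.5, 80% power needs 128 participants. If d = 0.50 is instead measured in SDs of the change score, power is 0.29 whatever ρ is.

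**Step 5: effect detectable with 80% power, 17 per arm.** In change-score SDs it is 0.991. In raw-score SDs it is 0.991 × √(2(1 − ρ)):

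- ρ = 0.3: 0.991 × 1.183 = 1.17
- ρ = 0.5: 0.99
- ρ = 0.7: 0.991 × 0.775 = 0.77

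**Step 6: loss at T2, illustration only.** The article gives no expected loss. If 14 per arm had T2 data and ρ = 0.5, power would be 0.25 for d = 0.50 and 0.72 for d = 1.0.

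**The case against.** **The routine is not named.** This is correct, and N = 34 is not unique to the interaction routine. A paired t test with d = 0.5 also gives 34 (power 0.808, against 0.795 at 33). So a reader might infer that the article shows exactly which entry was made; it does not. The paired test is no rescue, however, because it tests change within persons and not a difference between the two conditions.

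**Some correlation gives 80%.** This is also correct, so it would be wrong to say that no reading reaches 80%. It takes ρ near 0.87–0.88, a value the article does not claim. At ρ = 0.87 its own input f = 0.25 would give power near 1.0, so the interaction calculation would not have called for 34.

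**The power may not be as low as 29%.** A reader might infer that the chance of success is under one in three in any case. The article does not fix ρ, so that cannot be said: power is 45% at ρ = 0.7 and 61% at 0.8.

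**The comparable study found d above 1.2.** A true effect of that size would be well covered (power 0.92 at ρ = 0.5). But the article attaches its 80% to d = 0.50 and calls that the expected effect.

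**A small sample is acknowledged, and detail may sit in the full protocol.** The Discussion ties the limited sample size to generalizability and does not withdraw the 80%. A wrong stated figure is not an omission that a fuller document would cure. An allowance for loss at T2 could well be in the full protocol, so its absence here is not part of the point.

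**Conclusion.** The point holds. The stated d, sample size and power are inconsistent. With 17 per arm, power for a between-group d of 0.50 is 29% for a single two-group comparison, for d on the change-score scale, and for the planned test at ρ = 0.5. On the raw-score scale the planned test runs from about 17% to 61% as ρ goes from 0 to 0.8. The trial as sized has 80% power for d of about 1.0 at ρ = 0.5.

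These figures assume two-sided alpha 0.05, equal baselines, equal variances and all 34 analysed at T2. The failure of the stated 80% does not depend on which routine was run: it needs only that the article does not assume a correlation near 0.87–0.88. The explanation of how the figure arose is likely but inferred. A reader might also conclude that the trial must enrol 128 participants. That does not follow: the error lies in the claim, and an accurate statement of power repairs it.

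**What to change.** In section 2.7, delete the statement that d = 0.5 is equivalent to f = 0.25, and replace the power claim with wording such as:

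> With 34 participants analysed at T2, the group-by-time test has about 29% power for a between-group d of 0.50 and 80% power for d of about 1.0, assuming a T1–T2 correlation of 0.5 (22% and d 1.17 at 0.3; 45% and d 0.77 at 0.7).

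Name the G*Power routine that was used. Add that the figures fall if participants who drop out during the intervention, who are not replaced, lack T2 data. If the sponsor in fact expects an effect near 1.0, the text should say so and give the grounds in place of d = 0.50. Do not quote power for a baseline-adjusted ANCOVA unless the primary analysis is changed to one, since that would again pair a power figure with a test the plan does not use.

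The cost is a rewording and a less favourable power figure. No participants, visits or analyses are added.

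### The group-by-time ANOVA on T1 and T2 is a change-score t-test: valid, but at plausible T1–T2 correlations less precise than analysing T2 SGATS adjusted for T1

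*Protocol article*

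**What the plan says.** Section 2.7 (Data analyses) of the protocol article fixes the primary test of the SGATS as a "two-way repeated measures ANOVA test to determine whether any change in response to the SGATS (i.e. the dependent variable) is the result of interaction" between type of treatment and time, where time is "our second factor T1 and T2". It mentions no adjustment for the baseline score. For the secondary scales it says only: "Changes between the groups at pre-test and post-test will be tested using ANOVA, while correcting for multiple testing".

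The same section states that "the proposed RCT sample required 34 participants", 17 per arm, from an effect of d = 0.5 described as the "equivalent of *f* = 0.25 ANOVA", and that this "had sufficient power (80%) to reject our null hypothesis". The significance level is given as "Statistical significance was set at *P* < .05".

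Table 2 (section 2.6) lists the SGATS at T1 and T2. Section 2.4 (Procedure) places T1 before allocation: "Once they completed the baseline questionnaires, the randomization procedure will start". Randomisation is stratified by gender, type of trauma and frequency of trauma, not by baseline SGATS.

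**The concern.** With one measurement before allocation and one after, the group-by-time interaction compares the mean change between arms and nothing more. This in effect fixes the coefficient on the T1 score at 1. Regressing T2 on arm and T1 estimates that coefficient from the data. Unless T1 and T2 are almost perfectly correlated, the estimated coefficient leaves less residual variance.

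Two things are at stake in a trial of 34. The first is precision, which is scarce with 17 per arm. The second is dependence on baseline luck: the arms can easily differ by chance on T1 SGATS, and a change score over-corrects for such a difference by regression to the mean. A valid pre-randomisation covariate is already collected, so the better analysis needs no new data.

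**Working it through.** **Inputs.** From section 2.7: N = 34 (17 per arm), d = 0.5, f = 0.25, 80% power, alpha 0.05 (sidedness not stated; the ordinary F test is used). From sections 2.4 and 2.6: SGATS at T1, before randomisation, and at T2. Not in the article: the T1–T2 correlation of the SGATS (rho), so a range is shown. Variances are in units of the SGATS variance, taken as equal at T1 and T2.

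**The plan's own figure.** For the interaction with m = 2 occasions, the noncentrality is lambda = f² × N × m / (1 − rho), on 1 and N − 2 degrees of freedom. With f = 0.25 and rho = 0.5, lambda at N = 34 is 0.0625 × 34 × 2 / 0.5 = 8.5. Power is 80.7%, and 34 is the smallest even total that reaches 80%. Other correlations do not return 34: N is 66 at rho 0, 46 at 0.3 and 22 at 0.7. So rho = 0.5 is back-solved, not stated.

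**Equivalence.** With two arms and two occasions, the interaction F on 1 and 32 degrees of freedom is the square of the unpaired t on T2 − T1.

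**Variance per person.**
- Change score: 2(1 − rho).
- ANCOVA: 1 − rho², times a penalty of about 1 + 1/30 = 1.033 for estimating the slope, on 31 degrees of freedom.
- Ratio: (1 + rho)/2 × 1.033.

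**Power at d = 0.5, 17 per arm.** Lambda = d² × N/4 / variance = 2.125 / variance.

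| rho (assumed) | Change variance | ANCOVA variance with penalty | Ratio | Power, change | Power, ANCOVA |
|---|---|---|---|---|---|
| 0.3 | 1.40 | 0.91 × 1.033 = 0.940 | 0.67 | 22% | 31% |
| 0.5 | 1.00 | 0.75 × 1.033 = 0.775 | 0.78 | 29% | 36% |
| 0.7 | 0.60 | 0.51 × 1.033 = 0.527 | 0.88 | 45% | 49% |
| 0.8 | 0.40 | 0.36 × 1.033 = 0.372 | 0.93 | 61% | 64% |
| 0.9 | 0.20 | 0.19 × 1.033 = 0.196 | 0.98 | 88.5% | 89.0% |

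The ratio reaches 1 at rho = 2/1.033 − 1, or about 0.93 to 0.94.

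**Precision at rho = 0.5.** The standard error for the change score is sqrt(2/17) × sqrt(1.00) = 0.343 SD, so the 95% CI half-width is 2.037 × 0.343 = 0.70 SD. For ANCOVA it is 2.040 × 0.343 × sqrt(0.775) = 0.62 SD. The effect detectable with 80% power falls from 0.99 SD to 0.859 × sqrt(1.033) = 0.87 SD.

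**Simulation, 20,000 trials per setting, change score against ANCOVA.** At rho 0.5 and d = 0.5, power is 28.9% and 36.4%. At rho 0.7 it is 43.9% and 48.6%, and at rho 0.9 it is 88.5% and 88.8%. With no effect and rho 0.5, the type I error is 4.8% and 5.0%.

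**Baseline imbalance.** The T1 difference between arms has a standard error of sqrt(2/17) = 0.34 SD. Given an imbalance of that size and rho = 0.5, the change-score estimate shifts by (1 − 0.5) × 0.34 = 0.17 SD, about a third of d = 0.5. ANCOVA largely removes this shift.

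**The case against.** The strongest reply is that nothing in the plan is wrong here. The interaction test is unbiased over randomisations and holds its level, and the stated 34 reproduces for exactly this test, so analysis and sample-size calculation agree. That stands: this is a gain in efficiency, not the correction of an invalid test.

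The size of the gain is also uncertain. T1 and T2 lie only a few weeks apart and the SGATS subscale alphas are 0.84 and 0.87, so a high correlation cannot be excluded. At rho 0.8 the gain is three points of power, and at 0.9 it is negligible. That stands too, and is why a range is given.

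A reader might infer that adjustment is free and better at every correlation. At N = 34 it is not: the slope costs about 3% of variance and one degree of freedom, and at rho 0.95 the variance ratio is 1.007.

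A reader might also infer that the baseline is always wasted. At rho 0.5 the change score has the same variance as T2 alone, and below 0.5 a larger one. Above 0.5 it does gain from the baseline, only less than ANCOVA does.

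The name of the test might suggest that arm is treated as a within-subject factor. Section 2.7 defines it as intervention or waiting-list group, so that reading fails.

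For the secondary scales, the article names only ANOVA with a multiplicity correction. The exact model may sit in the fuller plan, so no fault is claimed there.

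**Conclusion.** The point holds as an efficiency improvement to the primary analysis. At correlations from 0.3 to 0.7, ANCOVA has about 67% to 88% of the change-score variance and adds roughly 4 to 9 points of power at d = 0.5. At 0.5, the value that the sample size implies, the change score draws no precision from the baseline, and the variance ratio of 0.775 is worth about 1/0.775 − 1 = 29% more participants. The estimate also depends less on chance imbalance. These figures rest on an assumed correlation and on equal SGATS variances at T1 and T2.

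A reader might conclude that the change would rescue the sample size. It would not. At rho 0.5 and d = 0.5, power is still only about 36%. Equating the two noncentrality formulas gives f = d/4 for this interaction, so f = 0.25 encodes a T2 difference of 1.0 SD rather than 0.5. At 1.0 SD and rho 0.5, power goes from 80.7% to 89.4%. The mismatch between d and f is a separate and larger problem.

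**What to change.** In section 2.7, make the primary analysis a linear model of T2 SGATS total on arm, adjusted for T1 SGATS total, and report the adjusted mean difference with its 95% CI. Keep the group-by-time ANOVA as a sensitivity analysis. Use the same model, each with its own T1 score, for the secondary scales measured at T1 and T2. Rewrite the power paragraph for the new test, stating the assumed T1–T2 correlation and showing a range.

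The cost is a short rewrite of the analysis and power text, one degree of freedom and about 3% of variance. No extra participants, visits or data are needed, and SPSS, which the plan already names, fits the model. If the correlation turns out to exceed about 0.93 there is no gain, and the loss is trivial.

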## Discussion

3.

The objective of the present study is to outline the rationale, study design, and methods employed in the BLAME-LESS study, a two-arm randomized controlled trial (RCT) assessing the impact of a concise online psychoeducation programme. This programme aims to alleviate feelings of trauma-induced shame and guilt experienced by adolescents concerning their defense responses during and following instances of physical/sexual violence or sexual abuse. These experiences of physical/sexual violence or sexual abuse are recognized as severe adverse events with potentially enduring effects on the development of a child (Downing et al., 2021; Hughes et al., 2017). Equipping adolescents with reliable information and valid explanations of typical defense responses that may arise during and after physical/sexual violence or sexual abuse is crucial for their journey to recovery. Our newly developed online psychoeducation programme, BLAME-LESS, affords young survivors of physical/sexual violence or sexual abuse with the opportunity to explore fresh perspectives on their reactions to traumatic experiences. By attaining knowledge about the defense cascade, we hypothesize that the dysfunctional posttraumatic cognitions and emotions associated with their trauma will diminish. To achieve this, the current programme incorporated several established components widely recognized in evidence-based psychological treatment of trauma-related stress in children and adolescents.

The proposed study has several strengths. First, it aims to evaluate the effectiveness of an online psychoeducation programme. A recent meta-analysis (Rogers et al., 2017) revealed a wide range of evidence-based internet programmes. However, most of these programmes are not easily accessible to the public (Rogers et al., 2017). If the proposed randomized controlled trial demonstrates a reduction in trauma-related shame and guilt, the online psychoeducation programme BLAME-LESS will become publicly available. This will offer a cost-effective and user-friendly solution by providing evidence-based online intervention that is accessible and free to use. Second, the study employed an RCT design with a waiting-list control group. By including a waiting-list control group, we can assess the effectiveness of the intervention using a well-controlled design. Furthermore, the BLAME-LESS programme has the advantage of requiring minimal time commitment. It incorporates various modules that cater to different learning styles, including visual, auditory, and online reading activities. This allows for a comprehensive learning experience. If effective, the programme can be implemented during potential waiting periods for treatment or as a precursor to psychological intervention.

While this study exhibits particular strengths, it is not exempt from certain limitations. A constraint arises from the online delivery of the intervention, lacking the direct involvement of a therapist. However, it is crucial to note that the specific aim of the intervention is for it to be independently viewed by adolescents, without the need for direct therapeutic guidance. Additionally, the study relies on self-reported measures, which can lead to potential overestimation or underestimation of symptoms. Future research should also incorporate parental input into outcome measures and examine how incorporating a support system might contribute to treatment outcomes. Furthermore, the limited sample size and absence of follow-up assessments restrict the generalizability of the findings. We did not include follow-up procedures due to ethical concerns regarding the potential burden on subjects relative to the study’s objectives. It is crucial for future research to explore the generalizability of the results, investigate long-term effects, and examine the impact on trauma-focused treatment when incorporating the BLAME-LESS programme prior to such treatment. Finally, no psychometric properties of the SGATS questionnaire are known for the target population of this study.

However, the current study is valuable for clinical practice and public health. The results will help evaluate the added value of accessible and free online psychoeducation for adolescents suffering from trauma-related guilt and shame. By identifying ways to reduce feelings of shame and guilt, adolescent survivors of physical/sexual violence or sexual abuse may be more willing to seek help and disclose important trauma-related information, leading to better treatment outcomes.
